### Study design and procedure

This study is a multi-center, randomized, controlled trial involving two parallel groups: i) the VR-CET group, which benefits from virtual reality exposure preceded by CBT sessions, and ii) the CBT-only group (control group). Interventions take place over a 2-month (8-week) cycle, with a total of 8 sessions (Cf. Figure 1). Both groups receive 4 CBT group sessions in the first month, followed by either 4 supervised individual virtual exposure sessions for the VR-CET group, or 4 additional individual CBT sessions for the CBT-only group. Each session lasts one hour and a half. Once the 8 sessions have been completed (2 months), patients are followed up for 6 months, for a total of 8 months.

**Fig. 1 Fig1:**
[figure not shown]
Participant timeline

### Treatment groups

The first four CBT group sessions focus on understanding the effects of alcohol, assessing motivation to change, behavioral and emotional strategies, cognitive strategies, relapse prevention and assertiveness strategies. These sessions are conducted in a group setting by a trained psychologist and a trainee.

Participants are then randomized into two groups (M1): i) VR-CET + BT group, ii) CBT group only. Allocation is centralized, individualized and randomized according to the following factors: center, presence of pharmacological treatment to maintain alcohol abstinence (2 modalities), history of AUD treatment in the last five years (2 modalities), alcohol consumption goals (2 modalities) and severity of alcohol dependence according to DSM-5 criteria (3 modalities).

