
## Methods/Design

### Study setting and population

Study data will be collected in day hospitals (DH) within the addiction departments of public hospitals. For this research, four centers in the Paris area will be involved in recruiting patients. The four recruiting centers are: 1) Department of Addictions—Hôpital Albert Chenevier—CHU Henri Mondor—APHP – Créteil, 2) Department of Addictions—Hôpital Fernand Widal—Nord—Université de Paris—APHP – Paris, 3) Department of Addictions—Centre hospitalier des Quatre Villes – Sèvres, 4) Department of Addictions—Tolbiac Day Clinic – Paris. Recruitment will be done by the investigating physician at the time of admission to the DH during an individual consultation. If the patient is eligible for the study, the full protocol will be presented and reviewed during an individual consultation at the DH enrollment visit.

The following inclusion criteria apply: i) 18 to 80 years of age at the time of enrolment; ii) patients with a diagnosis of AUD according to DSM-5 criteria (American Psychiatric Association, 2013); iii) patients who had been abstinent for at least 15 days; iv) patients who can speak, understand and read French; v) patients who have signed an informed consent form and who are affiliated to a health insurance plan.

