Subjects are not included if they are: i) adults under legal protection or deprived of liberty by judicial or administrative decision; ii) pregnant or breast-feeding women; iii) patients with decompensated psychiatric disorders (psychotic disorders, mood disorders and anxiety disorders); iv) patients relapsing from their AUD; v) patients with severe cognitive impairment as defined by the MOCA Cognitive Assessment Test (score < 10) [24]; vi) visually impaired patients; vii) patients with contraindications to virtual reality exposure, due to epilepsy or history of photoparoxysmal EEG response, or vestibular disorders; viii) recent cardiovascular accident less than 3 months old, current nausea/vomiting, claustrophobia and moderate or severe myopia (greater than -3. 5 diopters); ix) patients wearing any of the following medical devices (due to the risk of interference with the virtual reality headset): pacemaker, implanted defibrillator or implanted hearing aid (non-implanted prostheses are not contraindicated if the patient agrees to remove them during VR-CET); x) participation in another study or being in the exclusion period after previous research involving human subjects; xi) and patients benefiting from State Medical Assistance (defined as access to healthcare for people in an irregular situation).

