### Criteria for discontinuing or modifying allocated interventions

Participants can end their participation in the research at any time, and the investigator may do so for safety reasons or in the best interest of the participant. Temporary break in participation may occur in cases of persistent psychological distress, trauma during sessions, or discomfort related to virtual reality. Early termination may occur if inclusion criteria are not met. Pregnancy, protective measures, or enrollment in another study will result in definitive dropout. Absence from group sessions (50%) may lead to exclusion.

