### Selection of participants for analyses

The intention-to-treat population will include all patients who signed the informed consent form and were randomized to one of the two study arms and will be analyzed according to the initial randomization group. The per-protocol (PP) population will include patients enrolled in the study without major deviations from the current protocol, including erroneous inclusion of patients, changes or noncompliance with the treatment assigned at randomization. The primary endpoint will be analyzed by ITT and secondarily by PP analyses. PP analyses. Secondary endpoints will be analyzed according to ITT and PP principles to ensure robustness of results.

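### Randomisation comes about a month after inclusion: no eligibility confirmation is stated at M1, an attendance exclusion is listed as a post-allocation rule, and drinking before M1 counts in the outcome unadjusted

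*Protocol article*

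**What the plan says.** All places are in the protocol article.

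- **Study setting and population.** Recruitment and eligibility belong to day-hospital admission: "Recruitment will be done by the investigating physician at the time of admission to the DH during an individual consultation". Inclusion requires "patients who had been abstinent for at least 15 days". Those not included are "iv) patients relapsing from their AUD", patients with VR contraindications (vii), patients with "recent cardiovascular accident less than 3 months old, current nausea/vomiting, claustrophobia" or more than mild myopia (viii), and wearers of certain implanted devices (ix). Items vii and ix are expressly tied to VR or the headset; viii reads as a continuation of vii.
- **Study design and procedure; Treatment groups.** Both groups have four group CBT sessions in the first month. Then: "Participants are then randomized into two groups (M1): i) VR-CET + BT group, ii) CBT group only". No condition is attached. VR exposure is confined to sessions 5 to 8.
- **Criteria for discontinuing or modifying allocated interventions.** "Absence from group sessions (50%) may lead to exclusion". The same section allows early termination when inclusion criteria are unmet and withdrawal for safety, and makes pregnancy a definitive dropout. None of these has a time point or is limited to one arm.
- **Selection of participants for analyses.** Intention-to-treat (ITT) keeps every randomised patient in the allocated arm. Per-protocol (PP) removes major deviations, including "changes or noncompliance with the treatment assigned at randomization".
- **Introduction; Primary outcome; Statistical methods.** The trial is open-label. The primary objective counts standard drinks to 8 months after enrolment, from monthly Timeline Follow-Back (TLFB). The main test is an unadjusted t-test; the complementary models adjust for the minimisation factors and the number of sessions.

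**The concern.** Randomising after a common first phase is a sound design, but it makes M1 the baseline of the comparison. Three things in the article still point to inclusion or to the period after allocation.

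1. **VR-related exclusions.** They guard against an exposure that starts only after M1, yet the only stated time at which they are judged is inclusion. Some of them can change within a month.
2. **The attendance rule.** It depends wholly on information complete at M1, but it is discretionary and is listed where the arm is already known. A choice that could be made blind to allocation may then be made with knowledge of it.
3. **Drinking between inclusion and M1.** Treatment cannot affect it, yet it enters the cumulative total and no analysis is stated to adjust for it.

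At stake are the completeness and balance of follow-up, the use of the PP analysis as a robustness check, and the precision of the primary comparison.

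**Working it through.** **Step 1: order of events.** Inclusion and eligibility, then group sessions 1 to 4 (month 1), then allocation (M1), then individual sessions 5 to 8 (to M2), then follow-up to M8. Group sessions occur only in the first block, so attendance at them is fully known when the allocation call is made.

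**Step 2: what a late attendance exclusion would do.** Suppose the rule is applied after allocation. The patient stays in the ITT set, so the primary set is not altered by definition. If participation ends, however, later TLFB data are missing and must be imputed, and the patient may also leave the PP set. Because the rule is optional and the arm is visible, both losses could differ by arm. Applied before allocation, neither can.

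**Step 3: a patient newly VR-contraindicated by M1.** In the control arm the assigned sessions can still be given. In the VR arm they cannot: the patient remains untreated in ITT and falls under the PP noncompliance clause.

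**Step 4: illustration of the dilution.** The article gives 65 per group, two-sided alpha 0.05 and power 0.80, but no mean difference or SD, so the 65 cannot be reproduced from its inputs. Solved backwards for a two-sample t-test, it implies a standardised difference d = 0.495. Suppose a share q of the VR arm gets no VR, has control-like outcomes and stays in ITT. The effect becomes d × (1 − q), with 65 analysed per arm:

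| VR patients affected (of 78) | q | d × (1 − q) | Power |
|---|---|---|---|
| 0 | 0 | 0.495 | 80% |
| 1 | 1.3% | 0.489 | 79.0% |
| 2 | 2.6% | 0.482 | 77.9% |
| about 4 | 5% | 0.470 | 75.9% |
| about 8 | 10% | 0.446 | 71.3% |
| about 12 | 15% | 0.421 | 66.3% |

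Every q is an assumption; the article supports none of them.

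**Step 5: drinking before M1.** If the total runs from enrolment, 1 of its 8 months (1/8 = 12.5% of the window) precedes randomisation. Write the total as A (inclusion to M1) plus B (M1 to M8). Randomisation makes the expected difference in A zero, so A brings no bias, only variance and chance imbalance. Linear adjustment for A multiplies the residual variance by 1 − r², where r is the within-arm correlation of A with the total. Assumed values: r = 0.3 gives 1 − 0.09 = 0.91, and r = 0.5 gives 1 − 0.25 = 0.75. The allocation factors are centre, abstinence medication, treatment history, consumption goal and AUD severity; A is not among them.

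**The case against.** - **Silence is not absence.** The article condenses a fuller protocol, and its timeline figure and assessment schedule are not shown. A reader might infer that eligibility is never re-checked; the text supports only that no re-check is stated. This stands. The early-termination clause does not settle the matter, since it is discretionary, undated and listed under allocated interventions.
- **Relapse.** A reader might infer that anyone who drinks before M1 is randomised in breach of exclusion iv. That does not follow. The criterion governs inclusion, and the Discussion says the trial aims at reduced consumption as well as abstinence. This stands in full.
- **One-sided loss.** A reader might infer that in general only the VR arm loses treated patients. Relapse, psychiatric decompensation and pregnancy can affect either arm, and the only VR-specific discontinuation item, discomfort, leads to a temporary break. One-sidedness covers new VR contraindications alone.
- **Rarity.** Epilepsy, claustrophobia and myopia are largely stable, and a past cardiovascular event becomes less recent with time. Shares of 5% to 15% would need about 4 to 12 of 78 patients to become contraindicated within a month. This stands, and the power figures are illustration only.
- **Attendance rule.** It may be meant to act before M1, where it does no harm. That is plausible, but its placement says otherwise, so the sections need reconciling.
- **ITT is primary.** This stands: dilution, not selection bias, is the main risk to the primary comparison, and PP exclusions for noncompliance always carry some risk of imbalance.

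**Conclusion.** The point holds as a matter of timing. Eligibility is tied to inclusion, allocation comes about a month later, and no confirmation at M1 is stated. The clearest defect is the optional attendance exclusion, placed among post-allocation rules although its facts are complete beforehand. It could produce arm-dependent missing data and PP exclusions, to an extent that cannot be calculated.

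New VR contraindications would dilute the ITT effect and unbalance the PP set. The size cannot be derived from the document and is probably small: one or two patients would cost about 1 to 2 percentage points of power, assuming d = 0.495, 65 analysed per arm and no benefit without VR. The lower rows of the table are not estimates of what will happen.

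Drinking before M1 breaches no criterion and does not bias the ITT comparison. It is unadjusted noise in the primary outcome. This rests on the Introduction's wording that the 8 months run from enrolment; the Primary outcome section gives no start date for the count.

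**What to change.** 1. **Reconcile** Study setting and population, Treatment groups, and the discontinuation section. The existing VR-related exclusions should be confirmed, and the existing attendance rule applied as a fixed yes/no, before the allocation call and not after it. The content of these criteria need not change. If the full protocol already does this, a sentence in the article suffices.
2. **Add a covariate.** Include TLFB consumption from inclusion to M1 as a pre-randomisation covariate in the adjusted analysis of the primary outcome. Monthly TLFB collection should already supply it.

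Cost: a protocol amendment, a short checklist in the randomisation form, and one model term. A few included patients would not be randomised, so recruitment may take slightly longer. Losses before M1 cannot unbalance the arms.

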### Evaluation outcomes

#### Primary outcome

The primary outcome is the cumulative number of standard drinks consumed (in grams of pure alcohol) at 8 months, as reported by patients. As a reminder, in France, 1 standard drink = 10 g of pure alcohol = 1 unit of alcohol [25]. Alcohol consumption is estimated retrospectively by patients every month using the Timeline Follow-Back (TLFB) method, a widely used method that has demonstrated good psychometric properties and superiority over free recall [26]. This method allows retrospective estimation of alcohol consumption over a specified period of up to one year. Estimates of alcohol consumption (in standard drinks) are collected monthly by the research team, either in person or by telephone, to reduce recall bias and improve the performance of this method over time [27].

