#### Secondary outcomes

Craving is assessed by the Transaddiction Craving Triggers Questionnaire (TCTQ) [28]. This is an instrument designed to assess what triggers craving. The questionnaire is completed at inclusion, M2, M5, and M8. Craving is also assessed using a VAS (0 to 10) at each exposure session [29] and on a monthly basis after M2, in the same way as for the primary outcome.

The frequency of hazardous drinking episodes is assessed with the AUDIT-C (Alcohol Use Disorders Identification Test) questionnaire [30], an abbreviated version of the AUDIT self-report questionnaire [31] that includes three questions about the patient's alcohol consumption. These data are collected at enrollment and at treatment phases M2, M5, and M8. Finally, reported alcohol consumption is correlated with weekly DH toxicology monitoring, if this is routinely performed at the recruiting centers. Weekly toxicology screenings for ethyl glucuronide (EtG), if performed as part of the routine care at the recruiting centers, will be recorded in the logbook.

Anxiety is assessed by the Generalized Anxiety Disorder-7 (GAD-7) questionnaire [32]. This instrument is designed to screen for generalized anxiety disorder and may also help to identify panic disorder, social anxiety disorder, and posttraumatic stress disorder. It is administered at inclusion, M2, M5, and M8.

Depression is assessed by the Patient Health Questionnaire-9 (PHQ-9) [33]. This instrument collects information on the presence and intensity of depressive symptoms. Data is collected at inclusion, M2, M5, and M8.

Self-efficacy is assessed by the Sense of Self-Efficacy Questionnaire, originally developed in German by Matthias Jerusalem and Ralf Schwarzer [34]. It is administered at inclusion, M2, M5, and M8.

Rumination is assessed by the 15-item Perseverative Thinking Questionnaire (PTQ). This is a widely used self-report measure of repetitive negative thinking [35]. It is administered at inclusion, M2, M5, and M8.

The state of presence in virtual reality is measured by the QEP questionnaire (Questionnaire sur l'État de Présence) developed by the UQO Cyberpsychology Laboratory (2002) [36, 37]. This survey is conducted at M2 for the participants randomly assigned to the VR-CET group.

Cybersickness risk is assessed after each VR-CET session using the Cybermalaise Questionnaire from the UQO Cyberpsychology Laboratory [38].

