All questionnaires are completed by DH patients at inclusion and M2. The scheduled assessments from M3 to M8 are conducted by telephone (Cf. Table 1).

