### Statistical methods

The characteristics of all patients will be described globally and according to their randomization group, using the number of patients (%) for qualitative variables and the median [interquartile range] or mean (± standard deviation) for quantitative variables, depending on the normality of their distribution. A patient flow diagram will be generated. Results are reported according to CONSORT recommendations. Tests will be two-tailed, and a significance level of *p* < 0.05 will be considered statistically significant. The primary outcome (self-reported cumulative number of standard drinks consumed at 8 months) will be compared between the two groups using Student's t-test for independent samples. Complementary analyses will be conducted using generalized linear regression models adjusted for minimization factors and number of sessions per setting. Given the repeated measurement of outcomes and the multicenter design of the study, additional analysis will be performed including Cox and mixed models. To consider Survival analysis will also be conducted using a linear mixed model. Secondary endpoints will be analyzed using the same methodology as for the primary endpoint, i.e. a comparison of the mean using the usual tests. primary endpoint, i.e. a comparison of means using standard tests at 8 months. Secondary analyses to assess changes in secondary endpoints will be performed using evaluated using linear mixed models.

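### No questionnaire is listed at M1, when patients are randomised, so change from inclusion mixes shared and randomised treatment and adjusted secondary analyses lose some precision

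*Protocol article*

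**What the plan says.** Under Study design and procedure the protocol article states: "Both groups receive 4 CBT group sessions in the first month". The arms then diverge into four individual virtual-reality exposure sessions or four individual CBT sessions. Under Treatment groups, after describing the shared sessions, it says: "Participants are then randomized into two groups (M1", which places allocation at month 1.

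Under Secondary outcomes the schedule is given instrument by instrument. For the craving-trigger questionnaire (TCTQ): "The questionnaire is completed at inclusion, M2, M5, and M8". GAD-7, PHQ-9, the self-efficacy questionnaire and the PTQ have the same four time points. The section closes with "All questionnaires are completed by DH patients at inclusion and M2" and "The scheduled assessments from M3 to M8 are conducted by telephone". Craving on the visual analogue scale is planned "at each exposure session [29] and on a monthly basis after M2", and the exposure sessions come after allocation. Drinking differs: "Alcohol consumption is estimated retrospectively by patients every month using the Timeline Follow-Back (TLFB) method".

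Under Statistical methods, the main analysis of each secondary endpoint compares means at 8 months by standard tests, with no baseline term named. In addition: "Secondary analyses to assess changes in secondary endpoints will be performed using evaluated using linear mixed models". The adjusted regression models name the minimisation factors and the number of sessions, but no baseline score.

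**The concern.** The randomised part of the trial starts at M1. The only questionnaire scores that precede it were taken about a month earlier, before four sessions of CBT common to both arms and early in abstinence (entry requires only 15 days). The next reading, at M2, follows the randomised sessions.

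Two things are at stake for craving, anxiety, depression, rumination and self-efficacy, which are the secondary objectives. First, a change from inclusion to M2 within an arm contains a shared month and a randomised month that cannot be separated. Improvement in the VR-CET arm that preceded allocation could be reported as if it followed VR. Second, a score taken just before allocation usually predicts later scores better than one taken before the shared treatment, so a model that uses baseline information would be more precise with it.

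**Working it through.** **Plan's own figure.** The article gives none on this point: no correlations between visits and no standard deviations for these scores. All correlations below are therefore assumptions.

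**Step 1, timing.** Inclusion: questionnaires. Month 1: shared CBT. M1: allocation, no questionnaire listed. Month 2: randomised sessions. M2, M5, M8: questionnaires. Between inclusion and M2 there is no reading that divides the shared from the randomised month.

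**Step 2, bias.** Simulation with 4,000 runs and 65 per arm:
- inclusion score standard normal;
- M1 = 0.6 × inclusion − 0.5 + noise (SD 0.8), where −0.5 is the shared CBT effect;
- M8 = 0.6 × M1 − 0.3 − 0.3 × (VR arm) + noise (SD 0.8), so the true effect is −0.30.

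Mean between-arm estimates were −0.299 (t-test), −0.294 (difference in change from inclusion), −0.297 (adjusted for inclusion) and −0.297 (adjusted for M1). None is biased. The control arm's mean change from inclusion was −0.60. By construction −0.50 of this is the shared phase, and 0.6 × (−0.5) − 0.3 − (−0.5) = −0.10 is the change from M1 to M8. So the mixing affects within-arm change and leaves the contrast alone.

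**Step 3, precision.** Let r0 be the correlation of inclusion with the outcome visit, r1 that of M1 with the outcome visit, and r01 that of inclusion with M1. Relative to an unadjusted comparison (residual variance 1):
- inclusion only: 1 − r0²
- inclusion plus M1: 1 − (r0² + r1² − 2·r0·r1·r01)/(1 − r01²)

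Assume correlation a + b·g^t at t months apart. Example, (a, b, g) = (0.3, 0.5, 0.9) at M8: r01 = 0.3 + 0.5 × 0.9 = 0.75; r0 = 0.3 + 0.5 × 0.9^8 = 0.5152; r1 = 0.3 + 0.5 × 0.9^7 = 0.5391. Inclusion only gives 0.7345, both scores give 0.6812, and the reduction is 1 − 0.6812/0.7345 = 7.3%.

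| (a, b, g) | M8, inclusion only | M8, both | Reduction M8 | Reduction M5 | Reduction M2 |
|---|---|---|---|---|---|
| (0.2, 0.5, 0.8) | 0.919 | 0.891 | 3.1% | 6.3% | 17.8% |
| (0.3, 0.4, 0.85) | 0.833 | 0.786 | 5.6% | 9.1% | 17.9% |
| (0.3, 0.5, 0.9) | 0.735 | 0.681 | 7.3% | 11.7% | 22.2% |
| (0, 0.8, 0.9) | 0.881 | 0.844 | 4.3% | 9.1% | 23.0% |

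At M8 a 3-7% reduction is worth 156/0.97 − 156 = 5 to 156/0.93 − 156 = 12 patients. In the same table, adjusting for the inclusion score alone already removes 8% (1 − 0.919) to 27% (1 − 0.735) of the unadjusted variance at M8.

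**Step 4, sensitivity.** If the shared CBT reorders patients strongly, M1 could matter more. With assumed pairs (r0, r1) from 0.3/0.4 to 0.5/0.7, using inclusion instead of M1 costs the equivalent of 8% to 47% more patients at M8. With smooth decay, r1 = r0^(7/8) and r0 from 0.3 to 0.7, it costs 3.6% to 9.8%. The size follows the assumption.

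**Step 5, patients already past M1.** As a rough guide, if half the patients had an M1 score (an assumption), the 3-7% at M8 would fall to about 1.5-3.5%.

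**The case against.** The main planned secondary test compares M8 means without a baseline, so a missing M1 score costs it nothing. The secondary objectives are timed at 8 months, where the gain is smallest. They concern a strategy that combines VR-CET with CBT, so counting from inclusion is defensible. The article nowhere says that within-arm change will be credited to VR alone. All of this stands, and it keeps the point minor.

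Four stronger readings are tempting, and the documents do not support them:
- *The treatment effect is biased.* The shared month precedes randomisation and cancels between arms (Step 2).
- *Every between-arm comparison loses precision.* This applies only to mixed models and baseline-adjusted analyses of the questionnaires. Drinking is recorded monthly, so a month-1 value should exist.
- *The loss is 8-14%.* That figure comes from assuming equal correlation r of 0.4 to 0.6 between all visits, with 1 − 2r²/(1 + r) set against 1 − r². Under that assumption an older score predicts as well as a fresh one, so the gain is only that of a second reading and says nothing about the age of the baseline.
- *Balance cannot be shown.* Inclusion scores are pre-randomisation and can be tabulated by arm.

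Finally, the schedule table and timeline figure are not shown, so an M1 entry there cannot be excluded. The text speaks against it, since it names time points for each instrument and none is M1.

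**Conclusion.** The point holds as a minor design weakness confined to the secondary questionnaire outcomes. Validity is intact and the primary outcome is untouched. What is lost is a clean reading of change over the randomised phase, plus some precision in mixed-model or baseline-adjusted analyses: about 18-23% of residual variance at M2, 6-12% at M5 and 3-7% at M8 under the four decaying structures, and less once patients without an M1 score are counted. These sizes rest entirely on assumed correlations. They would be larger if the shared CBT changed patients' ranking markedly. Analysis alone cannot recover an M1 score that was not collected.

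**What to change.** For patients not yet randomised, add TCTQ, GAD-7, PHQ-9, self-efficacy and PTQ at the last group session, before allocation. Adjust the M8 comparison of each score and its mixed model for the pre-randomisation scores: the inclusion score for everyone, plus the M1 score where available, with M1 otherwise treated as a missing baseline covariate. Describe change over the randomised phase from M1, and label change from inclusion as covering shared plus randomised treatment. If the schedule table already contains M1, align the Secondary outcomes text with it.

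Cost: a protocol amendment with the sponsor approval and ethics opinion that the article requires for substantial changes, and one more round of five short questionnaires at a session patients already attend. No new visit is needed. Patients already past M1 will have no M1 score. Adjusting for the inclusion score needs no new data and can be done regardless.
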